**Fig. 2 Fig2:**

The modified stepped-wedge randomized trial across three waves. CSC, Coordinated Specialty Care; ACC, Attention Control Condition; FAMES, Family Motivational Engagement Strategy; CFI, Cultural Formulation Interview

After site randomization, each CSC program will be allotted 18 months to recruit participant dyads to receive the ACC during the control phase, after which sites will participate in a three-month pre-implementation phase to commence training of family peers, program directors, and family education and support providers, followed by a 30-month active implementation phase to recruit a new cohort of participant dyads to receive FAMES (Fig. 2).

### Family member and client participant dyads

A total of 450 participant dyads will be recruited across nine CSC programs, with 225 participant dyads to receive the ACC and 225 to receive FAMES. Each participant dyad will include a family member and a loved one enrolled in CSC for FEP. Family member inclusion criteria are as follows: (1) one family member/support person of a client enrolled in CSC for ≤ 6 months; (2) ≥ 18 years of age; and (3) during the active implementation phase, did not participate in the ACC. Client inclusion criteria include the following: (1) ≥ 15 years of age, and (2) enrolled in CSC for ≤ 6 months. Potential participants will be excluded if they do not understand the consent and assent process, and if they are non-English or non-Spanish speaking adults or youth.

### FAMily Motivational Engagement Strategy (FAMES) intervention

FAMES uses context-based communication strategies to enhance the clinical encounter by targeting theoretically informed mechanisms to engage family members in CSC [49]. Participants in the FAMES condition will be assigned to a trained family peer who will deliver FAMES across 12 weeks. FAMES is intended to be a brief intervention consisting of weekly contact (i.e., phone, text messages, email) delivered across three phases: (1) Building, (2) Continuous Contact, and (3) Family Peer Connection Community.

During the Building Phase (weeks 1–4), the first two appointments, lasting approximately 30 min, place an emphasis on building trust and rapport by integrating a modified version of the Cultural Formulation Interview (CFI) to identify and discuss cultural and contextual factors unique to each family member [37]. Example questions include the following: “what aspects of their background or identity can make their experiences better or worse in this clinical setting and in the community?” or “what types of help, resources, treatment were useful and not useful?” or “are there any kind of stressors that make your experience worse, such as living environment, discrimination?” On a scale of 1 = not important to 10 = high importance family members will rate their perceived level of importance in four domains: (1) addressing challenges with their loved one, (2) finding ways to manage stressors, (3) integrating cultural identity into sessions, and (4) developing coping skills specific to culture. Family peers will then use the information gathered to assist family members with setting goals for future FAMES appointments and during CSC team meetings to inform family psychoeducation appointments with providers. The next two appointments focus on coping skills that match those identified using the CFI and communication skills that build competence and empower family members to advocate and share their needs with others.

The Continuous Contact Phase (weeks 5–12) consists of eight semi-structured brief check-ins, lasting approximately 20 min, to capitalize on the strength of family peer roles to engage families while providing the space for participants to raise topics of discussion most relevant to them, and inquire about domains of importance identified during the Building Phase [50]. As an extended component of CSC, information obtained by family peers during the Building and Continuous Contact Phases, will be shared within CSC team meetings and with family education and support providers to improve the relevancy of family psychoeducation sessions.

Family Peer Connection Community Phase will occur during weeks 10 and 12. Family member participants will be invited to attend virtual group sessions and be given access to a closed online FAMES Facebook group, facilitated by family peers from CSC sites, where they will be able to connect and share experiences with co-participants.

### CUlturally Responsive Approach to Targeting Equity (CURATE) implementation package

Informed by the Theoretical Domains Framework, CURATE involves a combination of implementation strategies and content to target four domains of behavior change [51–53]: knowledge, skills, social identity, and social influence. To target these domains, CURATE includes a combination of strategies and content integrated across the pre-implementation and active implementation phases [54, 55]. The implementation package will consist of four discrete implementation strategies (distribution of educational materials, ongoing training, creating a learning collaborative, and auditing and providing feedback) from the Expert Recommendations for Implementing Change (ERIC) taxonomy and two persuasive communication approaches (storytelling and photovoice), often used in disparities research [56–59].

#### Pre-implementation phase

Educational materials on FAMES (e.g., guide, checklists) will be distributed electronically and by mail to family peers, program directors, and family education and support providers. An online digital learning platform will house a document library consisting of FAMES educational materials, digital storytelling videos sharing experiences from diverse family members, narrated videos outlining the delivery of FAMES, as well as how-to guides. The online learning environment will facilitate ongoing training across five weeks consisting of assigned weekly written and pre-recorded modules and weekly 90-min virtual training for discussion of assigned modules. Modules 1 and 2 that will embed equity-driven content (i.e., positionality, structural competency) and incorporate storytelling and community-based photovoice activities focused on understanding personal qualities that influence clinical encounters with family members [60, 61]. Modules 3 and 4, which cover components and delivery of FAMES include the use of the modified CFI, conceptualization, and integration within CSC. Module 5 will outline fidelity and monitoring of FAMES. Program directors and family education and support specialists will complete the self-paced online weekly modules. Family peers will complete the online modules and participate in the weekly virtual training sessions.

Following the 5-week didactic training, each family peer will complete two practice assessments over the course of two weeks with “participant actors” who will be pre-identified individuals with family members’ lived experience from diverse backgrounds (e.g., ethnoracial group, spirituality). Family peers will receive immediate feedback after each practice assessment from participant actors and two members of the study team, as well as written feedback in the form of a fidelity summary outlining skillfulness, adherence, and integration with CSC.

#### Active-implementation phase

A virtual learning collaborative will be created across all sites consisting of family peers. Learning collaborative meetings will be held bi-monthly with two members of the study team to provide a space for support and encouragement from family peers and to share successes and implementation barriers. Each meeting will also include specific learning topics (e.g., burnout, secondary trauma, cultural considerations) to facilitate ongoing training.

### Attention control condition

Family member participants in the ACC will receive weekly automated messages for 12 weeks based on participant communication preference (email, text message). Messages will include positively framed messaging informed by other text messaging-based studies [62, 63], along with educational materials about psychosis, tips (e.g., communication, de-escalation), a list of community-based and online resources and events, and reminder messages for upcoming appointments. Automated messages are outlined in Additional file 2 in the Supplementary Materials.

### Participant recruitment

CSC staff at each site will place recruitment materials in waiting rooms, within intake packets presented to clients and family members, and presented to all families enrolled in services no longer than 6 months. Interested family member participants may contact the research team directly or inform CSC staff of their interest. Research staff will also contact family members who have given CSC staff permission to share contact information. All potential participants will be screened by research staff for eligibility and those who are not eligible will be provided with a list of peer resources available in their community and online. Research staff will review and electronically send the consent form via the Research Electronic Data Capture (REDCap) e-consenting platform to all eligible participants by phone or video conference.

### Data collection procedures

Family members in the ACC and FAMES conditions will complete quantitative assessments at baseline, months 1–3, and at follow-up (3 months post-intervention), whereas client participants will complete assessments at baseline, month 3, and at follow-up. Figure 3 displays the SPIRIT diagram outlining the schedule of measures across the study period. All assessments will be collected by research staff over the phone and entered directly into REDCap. For participants who prefer to complete assessments on their own, SMS or link-to-text survey features in REDCap will be enabled to capture responses. For completing all assessments, family member/support person participants will receive a total of $275 and client participants will receive a total of $110.

**Fig. 3 Fig3:**
[figure not shown]
SPIRIT diagram: schedule of enrollment, interventions, and assessments

Table 1 provides a description of all study measures completed by participant dyads to assess primary and secondary outcomes and mechanisms of change. Measures with accessible versions in the Spanish language will be used, and if not, will be translated into Spanish.

**Table 1 Tab1:** Effectiveness outcomes: study assessments for primary, secondary, and mechanisms

Construct	Measure	Data Source	Timepoint
*Primary outcome*	**Engagement in CSC Family Psychoeducation (Aim 1)** will be measured as first session attendance rate and total attendance rate per family	Administrative data	Monthly
	**Engagement in FAMES (Aim 2)** will be measured by FAMES session attendance rate and the total number of contact minutes with participants by videoconference, in-person, and phone, and # of encounters by email, and text	Family peer survey	Weekly
*Secondary family outcomes*	**Perceived Stress (Aim 1)** will be assessed using the *Perceived Stress Scale*, which contains 10 Likert-style items to assess the degree to which an individual appraises life as stressful	Family participant survey	BL, 3 m, FU
	**Anxiety (Aim 1)** will be assessed using the *General Anxiety Disorder-7 item* [64]*.* Scores 8 or greater is cut-off for anxiety disorder	Family and client participant survey	BL, 3 m, FU
*Secondary client outcomes*	**Client Engagement in CSC (Aim 1)** will be measured as the client attendance rate in CSC	Administrative data	Monthly
	**Depression (Aim 1)** will be measured using the *Patient Health Questionnaire-9 item* [65]. A score of 10 or greater is cut-off for depression	Client participant survey	BL, 3 m, FU
	**Psychosis (Aim 1)** will be measured using *Community Assessment of Psychic Experiences – Positive 15-items Scale* [66]	Client participant survey	BL, 3 m, FU
*Mechanisms*	**Self-Efficacy (Aim 2)** will be measured using the 10-item *General Self-Efficacy scale* [67]. Scores range from 10 to 40, with higher scores indicating greater self-efficacy	Family participant survey	BL, Monthly
	**Connectedness (Aim 2)** will be assessed using the *Social Connectedness subscale of YSS-F* [68, 69], which assesses social support. Scores range from 4–20 where higher scores indicate greater social connectedness	Family participant survey	BL, Monthly
	**Motivation (Aim 2)** will be assess using the 26-item *Treatment Motivation Questionnaire t*o assess motivation about services	Family participant survey	BL, Monthly
**Other indicators (to be used as covariates/independent variables in analyses if Aims 1–2)**			
*Individual characteristics*	**Family member and client characteristics** will be assessed using modules from the *PhenX Toolkit Social Determinants of Health Core and social determinants of health*. Age, gender identity, sex, race, ethnicity, education, employment, marital status, religious preference, health insurance, etc	Family & client participant survey	BL
*Contextual factors*	**Contextual factors** will be assessed using the *Citizenship Measure* is a 46-item that measures community connectedness and engagement [70]	Family participant survey	BL
*Program characteristics*	**Program characteristics** will include setting, location, # of team members	Provider survey	BL

*BL *baseline, *PRE *pre-implementation phase, *FU *3-month post follow-up

Implementation outcomes are guided by the extension Reach, Effectiveness, Adoption, Implementation, Maintenance/Sustainability (RE-AIM) extension framework which identifies indicators related to sustainability and health equity-related considerations for tracking each domain of RE-AIM [71–74]. Table 2 outlines all measures to capture implementation outcomes which will be completed by family peers and CSC providers (i.e., family peers, program directors, and family education and support providers). Research staff will email participating CSC providers a unique REDCap link to complete pre- and post-training surveys during the pre-implementation phase. A longitudinal qualitative research approach will be used to explore potential barriers and facilitators to delivery and engagement that may inform modifications to implementation over time and understand experiences over time during the active implementation phase [77–79]. Semi-structured qualitative interviews will be scheduled and conducted via videoconference (i.e., Zoom) with family peers at baseline (end of pre-implementation phase) and at 6, 12, and 24 months after the commencement of the active implementation phase. Interviews will also be conducted with family education and support providers and/or program directors at baseline and at 12 and 24 months after the commencement of the active implementation phase. All interviews will be audio recorded, transcribed verbatim, and reviewed for accuracy.

**Table 2 Tab2:** Implementation outcomes: study assessments

Construct	Measure	Data source	Timepoint
*Implementation outcomes*	**Reach of FAMES (Aim 3)** will be measured as the % (and number) of participants who enroll in FAMES out of the # of service users identified at intake. Reach will be categorized by demographic characteristics (e.g., race, ethnicity, SES, distance from CSC). Interviews with family peers and providers will assess potential reasons for stronger or weaker reach	Provider survey, administrative data, and interviews	Monthly
	**Adoption (Aim 3)** will be measured as the % of family psychoeducation sessions that integrate information gathered from FAMES	Provider survey	Monthly
	**Competence of Family Peers (Aim 3)** will be assessed using five-item rater scale developed by the team and informed by previous research [75] for such topics as active listening, exploring barriers to engagement, incorporating prior information into current session, setting goals	Practice assessment and FAMES sessions	PRE, 12 m, 18 m, 24 m
	**Acceptability (Aim 3)** will be assessed using a feedback survey with multiple and short answer response items on satisfaction, will be administered after each live webinar session	Family peer and provider surveys	PRE
	**Knowledge (Aim 3)** will be assessed using a developed 10-item pre- and post- assessment embedded in the online training platform	Family peer and provider surveys	PRE
	**Implementation adaptations, barriers, and facilitators (Aim 3)** will be identified from longitudinal qualitative interviews	Family peer and provider interviews	PRE, 6 m, 12 m, 24 m
	**Sustainability of FAMES (Aim 3)** will be measured with the *Program Sustainability Assessment Tool* a 40-item scale to assess ongoing program support, funding capacity, and fit [76]	Provider survey, family peer and provider interviews	FU
**Other indicators (to be used as covariates/independent variables in analyses if Aims 3)**			
*Individual characteristics*	**Family peer and provider characteristics** will include role, education level, month/years of experience, race, ethnicity, sex, gender identity	Family peer, and provider survey	BL
*Program characteristics*	**Program characteristics** will include setting, location, # of team members	Provider survey	BL

*BL *baseline, *PRE *pre-implementation phase, *FU *3-month post follow-up

### Data analysis plan

All analyses will follow an intention-to-treat principle with participant data within clusters analyzed according to the cluster’s randomized crossover time. All quantitative analyses will utilize a type I error rate of *p* < 0.05. Multiple imputation will be used for missing secondary psychological outcomes, with separate imputations conducted by study phase and clinic, incorporating demographic variables to ensure the accuracy of imputed values under the assumption of missing at random. Analyses will be conducted using STATA version 14.2, R statistical software, or the Statistical Package for the Social Sciences (SPSS, version 31.0).

#### Aim 1: Impact of FAMES on primary and secondary outcomes

##### Quantitative data analysis

Statistical analyses for primary engagement outcomes will use Generalized Linear Mixed Models (GLMM) to compare engagement rates between the control (ACC) and intervention (FAMES), with a random effect for cluster (site), a fixed effect for each phase (ACC and FAMES), and a fixed effect for implementation wave to control potential time-related confounding [80, 81]. GLMM will also be used to assess change scores on secondary outcomes for family member and client participants from baseline to 3 months. Restricted maximum likelihood estimation with Kenward-Roger standard error and degrees of freedom correction to accommodate for our relatively small number of clusters will be used. Supplemental analyses will assess the likelihood of including relevant individual and program covariates (e.g., age, biological sex, race, and others) in models if significant differences among covariates occur between ACC and FAMES samples. Analysis of the secondary outcomes collected only from FAMES participants at follow-up will employ GLMMs to compare baseline to 3-month to follow-up inventory scores as a random effect repeated measures factor. Fixed effect covariates (e.g., age, biological sex, race, and others) will be included in these models as appropriate. A Bonferroni correction will be applied to primary engagement outcomes (first session attendance and total attendance per family and client) to control for multiple testing.

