## Methods

### Study design

This Hybrid Type 2 Effectiveness-Implementation trial will use a cluster-randomized modified stepped-wedge design (see Fig. 1). Nine CSC sites throughout the USA, in both rural and urban regions, will be randomized to one of three start dates (waves) [46, 47]. Each site will recruit participant dyads, comprised of family member/support persons and clients with FEP enrolled in CSC, with separate cohorts of participant dyads recruited into the ACC and FAMES conditions. Aim 1 (effectiveness) seeks to evaluate whether integrating FAMES improves family engagement in CSC compared to ACC. In Aim 2 (mechanisms of change), we will use quantitative survey data to examine whether our theoretically driven target mechanisms of connectedness, self-efficacy, and motivation mediate FAMES engagement. Aim 3 (reach, adoption, implementation, and maintenance) will use a concurrent (quan + QUAL) mixed methods approach to evaluate implementation through an equity-focused lens. This study follows the Standard Protocol Items: Recommendations for Interventional Trials (SPIRIT) reporting guidelines (see Additional file 1 in the supplementary materials for the SPIRIT checklist) [48].

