### Randomization

CSC programs will be randomized to one of three waves with different study start times offset by three months (Fig. 2). A two-stage stratified randomization procedure will be applied to account for differences in site size (large vs. small), using a median split by site panel size to designate sites as large or small. This block randomization method stratified by the size of the CSC program will ensure small and large sites have a balanced opportunity to receive the innovation at any point in the study timeline. To reduce the possibility of implementation contamination, study staff will perform each randomization incrementally at six months prior to the start date for the next wave.

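### The Aim 1 primary model relies on implementation wave to control time, but wave is constant within a site and removes none of the calendar drift from the FAMES effect

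*Protocol article*

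**What the plan says.** In the protocol article, Data analysis plan, Aim 1, the primary engagement outcomes are analysed by a generalized linear mixed model "with a random effect for cluster (site), a fixed effect for each phase (ACC and FAMES"), plus "a fixed effect for implementation wave to control potential time-related confounding". No calendar-time or period term is listed. The Aim 3 model, by contrast, does name fixed effects for time.

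Wave is defined twice. Under Study design, sites "will be randomized to one of three start dates (waves"). Under Randomization, "CSC programs will be randomized to one of three waves with different study start times offset by three months".

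The text with Fig. 2 gives every site the same sequence: "each CSC program will be allotted 18 months to recruit participant dyads to receive the ACC during the control phase"; then "sites will participate in a three-month pre-implementation phase"; "followed by a 30-month active implementation phase to recruit a new cohort of participant dyads to receive FAMES". The planned sample is 450 dyads, "with 225 participant dyads to receive the ACC and 225 to receive FAMES".

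The Power analysis section states power above 85% for Aim 1 with 450 participants, effect size 0.5, two-sided alpha 0.025 and ICC 0.01.

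**The concern.** A stepped-wedge comparison is protected against secular change only if the model separates treatment from calendar time. Here ACC precedes FAMES at every site, so any change in family attendance over the study period, whatever its cause, points along the same axis as the treatment effect. The term said to deal with this is a between-site factor, whereas the phase effect is estimated from within-site differences.

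This is not a detail left for a later document. The article names both the adjusting term and its purpose, and the term cannot serve that purpose. At stake is the primary estimate: drift could be reported as a FAMES effect or could hide one, while readers are told that it has been controlled.

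**Working it through.** **Inputs from the protocol.** Nine sites in three waves offset by 3 months; phases of 18 (ACC), 3 (pre-implementation) and 30 (FAMES) months; 225 + 225 dyads, so on average 25 + 25 per site; effect 0.5 SD, two-sided alpha 0.025 (critical value 2.241), ICC 0.01.

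**Assumptions.** Even recruitment within each phase, equal site sizes, a linear-model approximation on the standardized scale and a normal test. Drift rates are illustrative, because the protocol gives none.

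**1. The stated power.** A textbook cross-sectional stepped wedge with 3 sequences of 3 sites, 4 periods, categorical period effects and 450/(9 × 4) = 12.5 dyads per site-period gives SE 0.1505. Power = Φ(0.5/0.1505 − 2.241) = 86.0%. Simple design-effect calculations give 99.4% (m = 25, design effect 1.24) and 98.2% (m = 50, design effect 1.49). All are compatible with more than 85%, but only the period-adjusted layout lands close to it. That layout is neither the planned model nor the planned timeline.

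**2. The calendar gap.** Within each site the ACC midpoint is month 18/2 = 9 and the FAMES midpoint is month 18 + 3 + 30/2 = 36. The gap is 27 months in every wave. If FAMES enrolment fills in 24 months the gap is 21 + 12 − 9 = 24; if in 18 months, 21 + 9 − 9 = 21.

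**3. What the wave term does.** Generalized least squares (GLS) with a random site effect gives the SE of the phase coefficient and the weight that it places on a linear monthly trend:

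| Model | SE | Trend weight (months) |
|---|---|---|
| phase + wave (as planned) | 0.094 | 27.0 |
| phase only | 0.094 | 27.0 |

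The two rows are identical because phase lengths do not differ by wave. The SE can be checked by hand: √[(1 − 0.01)(1/225 + 1/225)] = 0.094. Wave therefore removes none of the drift.

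**4. Size of the distortion.** Bias b = (gap/12) × annual drift. Rejection under no FAMES effect = 1 − Φ(2.241 − b/0.094) + Φ(−2.241 − b/0.094).

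| Assumed drift | Gap 21 months | Gap 24 months | Gap 27 months |
|---|---|---|---|
| 0.05 SD/year | b = 0.0875; 10% | b = 0.100; 12% | b = 0.1125; 15% |
| 0.10 SD/year | b = 0.175; 35% | b = 0.200; 46% | b = 0.225; 56% |

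The nominal rate is 2.5%. A bias of 0.225 is 45% of the planned effect of 0.5.

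**5. Overlap.** Wave 1 starts FAMES at month 21. Wave 3 starts ACC at month 6 and ends it at month 24. Both conditions therefore recruit in the same calendar months only in months 21–24, when wave 2 is in pre-implementation.

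**6. Cost of adjusting for time** (30-month FAMES recruitment, ICC 0.01, power = Φ(0.5/SE − 2.241)):

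| Time term | SE | Power | Trend weight (months) |
|---|---|---|---|
| none (wave only) | 0.094 | 99.9% | 27.0 |
| linear calendar time | 0.195 | 63% | 0 |
| linear time, wave kept | 0.20 | about 60% | 0 |
| 6-month categories | 0.40 | 16% | 2.1 |
| 3-month categories | 0.465 | 12% | 0 |

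For linear time without wave, power is about 60% if FAMES fills in 18 months. At ICC 0.05 the results are almost unchanged.

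**The case against.** The strongest reply is practical. With three months of overlap no model has much concurrent information, so the limit lies largely in the design, and the textbook remedy of categorical calendar periods would leave power of about 12–16%. This stands, and it is why the remedy below uses a linear or low-degree smooth term and treats power as part of the change. It does not rescue the wave term: the precision of the planned model exists only because time is left out.

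The size is also conditional. The drift rates are assumptions, and 27 months is the upper end of the gap. Under Trial status, recruitment runs from May 2025 to October 2029, about 54 months, whereas wave 3 with a full 30 months would end at month 6 + 18 + 3 + 30 = 57. Hence the range of 21–27 months.

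Two other defences fail. Wave cannot be read as a calendar step, because Study design and Randomization both define it as the randomized start date. Analysing dyads by the cluster's randomized crossover time, as the intention-to-treat sentence has it, adds no time term.

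A reader might infer more than the protocol supports:
- That the trial becomes an uncontrolled before-after study. It does not: each site has an attention-control cohort, and non-concurrently controlled is the accurate description.
- That drift has been shown. The protocol reports none.
- That the secondary outcomes share the problem to the same degree. They are analysed as baseline-to-3-month changes, in which a drift in level largely cancels within person.

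**Conclusion.** The point holds for the Aim 1 primary engagement model. The statement that wave controls time-related confounding is wrong as written: the estimate and its SE are the same with or without wave, and linear calendar drift passes in full into the FAMES effect over a mean gap of 21–27 months. False-positive rates are about 10–15% at an assumed 0.05 SD per year and about 35–56% at an assumed 0.10 SD per year. These rest on linear drift, even recruitment and a normal approximation. The finding that wave does not help rests on none of the drift figures; it follows from the definition of wave and the common phase lengths.

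The stated power of more than 85% does not describe a time-adjusted analysis on this timeline.

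**What to change.** In the Aim 1 primary engagement model, add a prespecified term for calendar date of dyad enrolment, linear or low-degree smooth, alongside site and phase. Wave may be dropped. Report the wave-only model as a sensitivity analysis labelled as not adjusted for time.

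State that ACC and FAMES recruit concurrently only in about months 21–24, so the adjustment depends on the assumed shape of the trend, and that categorical calendar periods are impractical for this reason. A linear term is unbiased only if drift is linear.

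Restate the Aim 1 power for this model on the actual timeline: about 60–63% with linear time at ICC 0.01, effect 0.5 and two-sided alpha 0.025, and lower after small-sample correction.

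The change needs no new data beyond enrolment dates. Its real cost is a roughly doubled standard error (0.195/0.094 = 2.1) and a lower stated power. Recruitment is expected to run to October 2029, so the term can still be fixed well before analysis.
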